#### Sample size estimation

2.10.4

The sample size was calculated based on the primary outcome, defined as the clinical effectiveness rate. Drawing from prior studies and pilot data, the effectiveness rate for the conventional treatment group was estimated at 60%, while the moxibustion groups were hypothesized to achieve an effectiveness rate of 90%. A two-sided test was adopted with a significance level (*α*) of 0.05 and a statistical power (1-*β*) of 90%, ensuring adequate sensitivity to detect the specified effect size, the calculation yielded a minimum of approximately 24 participants per group. To accommodate an anticipated dropout rate of 20%, the sample size was adjusted upward to 30 participants per group. With three study groups, this results in a total sample size of 90 participants.

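### 24 per group does not give the stated two-sided 90% power for 60% versus 90%: about 42 per group are needed, and 24 gives about 70% for each pairwise comparison

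*Protocol article*

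**What the plan says.** Section 2.10.4 (Sample size estimation) gives every input needed to repeat the calculation:

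- Endpoint: "The sample size was calculated based on the primary outcome, defined as the clinical effectiveness rate".
- Control rate: "the effectiveness rate for the conventional treatment group was estimated at 60" per cent.
- Moxibustion rate: "the moxibustion groups were hypothesized to achieve an effectiveness rate of 90" per cent.
- Test: "A two-sided test was adopted", with "significance level (*α*) of 0.05".
- Power: "a statistical power (1-*β*) of 90" per cent.
- Result: "the calculation yielded a minimum of approximately 24 participants per group".

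The section then allows for 20% dropout, which gives 30 per group and 90 in total. It also describes the resulting sensitivity as adequate. No formula, software or multiplicity adjustment is named. Section 2.7 fixes allocation at 1:1:1. Section 2.10.3 names chi-square analysis among the tests for group comparisons.

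**The concern.** The inputs and the answer stand in the same sentence, and they do not agree. A difference of 30 percentage points is large, but a two-sided 5% test with 90% power still needs around 40 per group to detect it, and 24 is far below that.

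This calculation sets the size of the whole trial. It also supports the hypothesis in the Introduction that adding moxibustion is better than conventional treatment alone. If the 90% figure is wrong, readers will take the trial to be more sensitive than it is. A non-significant result could then be given more weight against moxibustion than the data can bear.

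**Working it through.** **Inputs.** p1 = 0.60, p2 = 0.90, difference 0.30, two-sided α = 0.05 and power 0.90 (section 2.10.4); equal allocation (section 2.7). So z₀.₉₇₅ = 1.960, z₀.₉₀ = 1.282 and (1.960 + 1.282)² = 10.507. The variances are 0.60 × 0.40 = 0.24 and 0.90 × 0.10 = 0.09, with sum 0.33. The mean rate is 0.75, so the pooled term is 2 × 0.75 × 0.25 = 0.375.

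**Attempt to reproduce 24 per group (one moxibustion arm against control).**

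| Formula | Calculation | n per group |
|---|---|---|
| Unpooled variance | 10.507 × 0.33 / 0.30² = 38.5 | 39 |
| Arcsine | h = 2·asin√0.9 − 2·asin√0.6 = 0.726; 2 × 10.507 / 0.726² = 39.9 | 40 |
| Pooled variance | (1.960√0.375 + 1.282√0.33)² / 0.30² = 41.7 | 42 |
| Continuity-corrected | (41.7/4)·[1 + √(1 + 4/(41.7 × 0.30))]² = 48.1 | 49 |

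None comes near 24. The gap is 15 to 25 per group, too large for rounding or choice of formula to explain.

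**Dropout step.** 24 / 0.8 = 30 and 3 × 30 = 90. Both are correct, so the error lies in the base number alone. The same step from 42 gives 42 / 0.8 = 52.5, so 53 per group and 159 in total.

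**Pairwise power at the stated sizes.** The normal approximation is Φ[(0.30 − 1.960√(0.375/n)) / √(0.33/n)].

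- n = 24: (0.30 − 1.960 × 0.1250) / 0.1173 = 0.469, power 68.0%.
- n = 30: (0.30 − 1.960 × 0.1118) / 0.1049 = 0.771, power 78.0%.

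Exact power was found by summing the binomial probabilities of all outcomes that reject:

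| Evaluable per group | Normal approximation | Exact, chi-square | Exact, Fisher |
|---|---|---|---|
| 24 | 68.0% | 71.2% | 60.2% |
| 30 (no losses) | 78.0% | 79.6% | 70.5% |

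**Other comparisons the section might have meant (two-sided 5%).**

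- *Three-group chi-square on 2 df, rates 60/90/90.* The mean rate is 0.80. The squared deviations are 0.04 + 0.01 + 0.01 = 0.06, so the noncentrality per participant is (0.06/3) / (0.80 × 0.20) = 0.125. With N = 72 the noncentrality is 9.0 and power is 77%. With N = 90 it is 11.25 and power is 86%. Reaching 90% takes 34 per group.
- *Both moxibustion arms pooled against control.* At 48 versus 24, power is 83.0% (normal), 85.2% (exact chi-square) or 79.5% (Fisher). At 60 versus 30 with no losses it is 90.0%, 91.5% or 88.7%. By the pooled-variance formula, 90% needs 31 per arm.

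**Where 24 might come from.** Values near 24 appear only under settings that conflict with those stated or are not described:

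- pairwise one-sided 5% with 80% power (22.7 unpooled, 23.5 arcsine, 24.7 pooled);
- pairwise two-sided with about 70% power (22.6 unpooled, 25.0 pooled);
- pooled moxibustion arms, one-sided at 90% power (25 per arm) or two-sided at 80% power (23 per arm).

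The document does not show which of these, if any, was used.

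**The case against.** The arithmetic itself is hard to contest. The best counter-argument is that the protocol does not say it is sizing a pairwise test. Section 2.10.4 refers to the moxibustion groups in the plural, and the hypothesis in the Introduction sets moxibustion plus conventional treatment against conventional treatment alone. If the two moxibustion arms are pooled, the shortfall at 24 per arm shrinks to about 5 points by exact chi-square (85% against 90%), instead of the roughly 20 points of the pairwise reading. This narrows the size of the error but does not remove it: 90% is not reached at 24 evaluable under any two-sided reading. Pooling reaches it only if all 90 are analysed, while the same paragraph plans for 20% loss, and by Fisher's test it falls just short even then.

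Three further points stand:

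- The origin of 24 cannot be established, so no single explanation should be pressed on the authors.
- The chance of missing the effect is about 30% for a single pairwise test with 24 evaluable, and nearer 20% if nobody is lost.
- Attaching 90% to the pooled contrast after the event could look like choosing a hypothesis to save a number. That contrast also says nothing about 15 versus 30 minutes.

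Multiple imputation of the primary outcome (section 2.10.3) does not rescue the claim. Even if it recovered everything lost, the result would be 30 per group and about 80% pairwise.

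**Conclusion.** The concern holds, and the stated figure is wrong as written. With the protocol's own inputs, each moxibustion-versus-control comparison needs about 42 evaluable per group (39 to 49 across standard formulas), not 24. Power at 24 is about 70%, and at 30 with complete data about 80%, by the uncorrected chi-square test. Fisher's test gives roughly 10 points less.

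These figures assume true rates of exactly 60% and 90%, independent binary outcomes and α = 0.05 for each comparison with no multiplicity adjustment. If the level were split to 0.025 for each of two comparisons (an assumption; the document does not state it), 50 per group would be needed before dropout. The pairwise size of the error depends on reading the calculation as one arm against control, but the failure to reach 90% at 24 evaluable per group does not. This must be corrected, because it is a false power statement for the primary outcome.

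**What to change.** Rewrite section 2.10.4 without changing N. Suggested wording: *With 30 participants per group, each comparison of a moxibustion group with conventional treatment (60% versus 90%, two-sided α = 0.05, chi-square test) has about 80% power with complete data and about 70% power if 24 per group are evaluable.* Remove the 90% claim for these comparisons, and name the formula or software used.

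If a 90% figure is to stay, say that it refers to pooled moxibustion against conventional treatment (60 versus 30), holds only if all 90 are analysed, and falls to 83% to 85% at 48 versus 24. Make clear that it does not bear on the 15- versus 30-minute comparison.

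The cost is one paragraph of wording and a less favourable power figure, with no extra participants. If the sponsor wants 90% power for each pairwise comparison, the protocol's own inputs imply about 53 per group after dropout, 159 in total.

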#### Safety assessment

2.10.5

Detailed records of any adverse events will be maintained, including the adverse event’s onset, symptoms, duration, severity, treatment, and disappearance. The incidence rate of adverse events will be calculated by recording the number of patients with adverse reactions and dividing it by the total number of patients. In the event of adverse reactions, clinicians must assess the necessity of trial discontinuation based on patient conditions. Serious cases are to be reported to the project management office of the supporting unit and the ethics committee within 24 h. The safety of moxibustion will be assessed at each treatment session.

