### Withdrawal criteria

2.6

If adverse drug reactions, acupuncture-related adverse events, significant physiological changes, or severe complications or deterioration of the condition arise during the research process, and a professional physician evaluates that continued participation is inadvisable, the researcher must terminate the study.The patient is noncompliant and refuses to adhere to the therapy regimen.Participant voluntarily requests to withdraw.

Researchers must diligently record the rationale and timing of individuals’ removal from the trial. Individuals who have undergone more than half of the treatment regimen (≥4 sessions) should be incorporated into the efficacy analysis.

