### Blinding

2.8

This study will not employ blinding for administrators and patients across different moxibustion groups due to the particular characteristics of moxibustion manipulation. However, this study will be blind to the group assignment of outcome assessors made by a specifically designated person.

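### The adverse event rate is defined by counting patients with adverse reactions, so patients whose recorded events are not attributed to treatment can drop out of it

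*Protocol article*

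**What the plan says.** Section 2.10.5 (Safety assessment) of the protocol article sets a wide net for recording: "Detailed records of any adverse events will be maintained". The details to be kept for each event are "onset, symptoms, duration, severity, treatment, and disappearance". The next sentence defines the summary measure, with patients who have adverse reactions as numerator and all patients as denominator: "The incidence rate of adverse events will be calculated by recording the number of patients with adverse reactions and dividing it by the total number". The section then uses the same word once more: "In the event of adverse reactions, clinicians must assess the necessity of trial discontinuation based on patient conditions". The article defines neither *adverse event* nor *adverse reaction*.

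Two other sections bear on the reading. Section 2.6 (Withdrawal criteria) opens its list with "If adverse drug reactions, acupuncture-related adverse events, significant physiological changes, or severe complications or deterioration of the condition arise". Section 2.8 (Blinding) states "This study will not employ blinding for administrators and patients across different moxibustion groups", but goes on to say that outcome assessors will be blinded to group. It does not say which of these people classify adverse events.

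**The concern.** One quantity has one name and a different numerator. An adverse event is ordinarily any untoward occurrence during the study, and an adverse reaction is one attributed to a treatment. Read literally, the formula takes a record of everything and reports only the attributed part, under the name of the whole.

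The distinction has some weight in this trial. The Discussion presents accidents during moxibustion as fairly common and names burns, infection and allergy in patients with reduced temperature sense. An infection in a patient with diabetes could be attributed either way. All three arms receive the same drugs, and only two receive moxibustion (section 2.9.2), so one route of attribution is closed to the control arm. A rate that depends on attribution could therefore fall short by different amounts in different arms, and a reader comparing 15 minutes, 30 minutes and control could not tell occurrence from attribution.

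**Working it through.** The article gives no adverse event figure, so there is nothing to reproduce. The check compares the texts and then illustrates the mechanism.

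**Step 1. Set the statements side by side (section 2.10.5).**
- Recorded: any adverse event, with no causal restriction.
- Name of the measure: incidence rate of adverse events.
- Numerator: patients with adverse reactions.
- Fields listed per event: six, and relatedness is not among them.
- Causality scale, causality step or causality assessor: none described.
- Between-arm safety test: none specified.

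The name and the numerator do not match. This is a formula the article states, not a detail it leaves out.

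**Step 2. Follow each reading.**
- *Reaction means attributed event.* Patients whose only events are not attributed are recorded but not counted. The formula also needs a classification that the listed fields do not supply, so someone would have to decide later which events are reactions.
- *Reaction is a synonym for event.* Nobody is dropped, and the fault is one of wording only.

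**Step 3. Write the relation.** Let p be the proportion of patients in an arm with at least one adverse event of any cause, and s the share of those patients with at least one event counted as a reaction. Then

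reported rate = p × s, and relative shortfall = 1 − s.

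The synonym reading is s = 1, with no shortfall.

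**Step 4. Illustration. Both p and s are assumptions, and neither comes from the article.** Take p = 30%, which is 9 of the 30 patients planned per arm (section 2.10.4).

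| s | p × s | Relative shortfall |
|---|---|---|
| 1.0 | 30% | 0% |
| 0.8 | 24% | 20% |
| 0.6 | 18% | 40% |
| 0.4 | 12% | 60% |
| 0.2 | 6% | 80% |

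**Step 5. Two arms, both with p = 30% (assumed).**
- s = 0.2 in control and 0.6 in a moxibustion arm: 30% × 0.2 = 6% against 30% × 0.6 = 18%, an apparent gap of 12 points.
- s = 0.4 in both: 12% against 12%, no gap.
- s = 0.6 in control and 0.2 in the moxibustion arm: 18% against 6%, the same gap reversed.

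The difference between arms depends wholly on the shares chosen. The example shows how the formula could mislead; it does not predict that it will.

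**The case against.** The strongest reply is that the two words are meant as synonyms. The section moves from one to the other inside a single sentence defining a single quantity, and its later sentence on discontinuation reads most naturally if *reactions* covers any untoward event. Vocabulary is loose throughout: the Discussion uses plain *adverse events* for harms it ascribes to moxibustion, and the Abstract uses *adverse effects*. With no relatedness field, the listed records could not by themselves support leaving unrelated events out. This stands as a plausible reading, and it is why the shortfall is a possibility and not an established fact. It does not rescue the sentence, which can still be applied literally by whoever programs the safety table.

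Section 2.6 does not settle the matter. It names drug reactions and acupuncture-related events, both attributed to treatment, and does not contrast reactions with events of any cause.

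A reader might go further and infer that unblinded staff, judging causality, decide the safety comparison. The article does not support that. It describes no causality judgement and no formal safety comparison, and section 2.8 blinds outcome assessors without saying who classifies events. A reader might also infer that the rate is too low in every arm. That would require *reaction* to mean attributed event and every arm to contain patients whose only events are unattributed; neither is established.

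Finally, an article may leave definitions of adverse events and relatedness to a fuller document. That is accepted: the absence of definitions is not the point here, only the mismatch within the stated formula.

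**Conclusion.** The point holds in limited form. Section 2.10.5 records any adverse event but defines the adverse event rate with patients who have adverse reactions as numerator. Under the usual meaning of *reaction*, the rate can be too low, and the shortfall could differ by arm because attribution to moxibustion is open only to the moxibustion arms. If the terms are synonyms, nothing is lost. The article gives no event figures and no causality procedure, so the size and direction of any bias cannot be stated; the 6% to 24% range and the 12-point gap are illustrations resting on assumed values. The primary outcome is not affected. The sentence should be corrected under either reading, because as written the reported figure may not be what its name says.

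**What to change.** Reword the sentence in section 2.10.5 so that the incidence of adverse events is the number of patients with at least one recorded adverse event, whatever its cause, divided by the number of patients in that arm. Naming the arm only makes explicit that the rate is reported by group.

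If relatedness is judged, report adverse reactions on a separate line, attributed to moxibustion or to the drugs, and state who makes the judgement and whether they know the allocation. If it is not judged, use *adverse event* throughout the definition and drop *adverse reaction* from it.

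The cost is one sentence and one table row. The any-cause rate needs no new data, since all events are already to be recorded. The reported adverse event rate may look somewhat higher than under the literal formula.

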**Methods:**

Participants will be randomly allocated to three clinical centers, with 30 individuals at each center, and evenly divided among the conventional treatment group, the 15-min moxibustion group, and the 30-min moxibustion group. The conventional treatment group will be administered mecobalamin and epalrestat for a duration of 4 weeks, while the moxibustion groups will receive moxubustion as an add-on therapy treatment twice a week over the same period. The duration of moxibustion differs from the 15-min group, while the procedure remains consistent across the moxibustion groups. The primary outcome is total clinical effectiveness. The second outcomes include electrophysiological examination, the Toronto Clinical Scoring System (TCSS), the Visual Analogue Scale (VAS), the Traditional Chinese Medicine Syndrome Score Scale (TCMS), and infrared thermography testing. The outcomes will be assessed during the baseline period, after the 8th treatment, and at the one-month follow-up.

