### Study design

2.1

This trial is a multi-clinical center, open method, randomized controlled trial (RCT), three-arm, parallel-group design. The study is designed to assess moxibustion as an add-on therapy to conventional treatment. This study protocol obtained approval from the Ethics Committee of the Third Hospital Affiliated with Zhejiang University of Traditional Chinese Medicine and has been registered with the Clinicaltrials registry (identification code: NCT06330233). This trial protocol is developed in accordance with the Standard Protocol Items: Recommendations for Interventional Trials (SPIRIT) guideline. The schedule of this trial is presented in Table 1, and the flow diagram of the study is shown in Figure 1.

**Table 1 tab1:** Schedule of enrolment, interventions and outcome assessments.

Study period	Baseline	Treatment phase (4 weeks)		Follow-up phase (1 month)
The time point	Week 0	Week 2	Week 4	month 1
Eligibility screening	√			
Demographic information	√			
Case data	√			
Inclusion criteria	√			
Exclusion criteria	√			
Moxibustion treatment		√	√	
Outcomes assessment				
(1) Total clinical effectiveness			√	√
(2) Electrophysiological examination	√		√	
(3) TCSS	√		√	√
(4) VAS	√		√	√
(5) TCMS	√		√	√
(6) Infrared thermography testing	√		√	
Safety evaluation		√	√	

√, required; TCSS, Toronto Clinical Scoring System; VAS, visual analog scale; TCMS, traditional Chinese medicine syndrome score scale.

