#### Moxibustion groups

2.9.2

Both moxibustion groups will receive the same conventional treatment (mecobalamin and epalrestat) as the control group, with moxibustion as an add-on therapy. In the 15-min moxibustion group, the selection of acupoints is based on traditional Chinese medicine literature (28), moxa cones will be pasted on the acupoints, and moxibustion will be applied by ignition, each time for 15 min at each acupoint, once every three days, twice a week, four consecutive weeks of treatment. To ensure standardization, the moxa cone will be kept at a distance from the skin that elicits a warm sensation without causing pain or burning, and this distance will be consistently maintained by the practitioner.

The 30-min moxibustion group will follow the same operation as the 15-min moxibustion group apart from the intervention duration.

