#### Secondary outcomes

2.10.2

Electrophysiological examination

The electrophysiological examination will be detected at week 0 and after 4 weeks of treatment (week 4). The latency, amplitude, motor nerve conduction velocity (MNCV), and sensory nerve conduction velocity (SNCV) of the tibial nerve and peroneal nerve of the lower extremities will be measured before and after treatment.

Toronto Clinical Scoring System (TCSS)

The TCSS is a valid instrument to reflect the presence and severity of diabetic peripheral sensorimotor polyneuropathy as measured by sural nerve morphology and electrophysiology (29). TCSS will be estimated at week 0, week 4, and month 1.

Visual Analogue Scale (VAS)

The level of pain at the subject’s lesion site will be determined using the VAS scale, which classifies pain on a scale of 0–10, with the greater the number the more pronounced the pain, i.e., a score of 0 indicates no pain, 1–3 represents mild pain, 4–6 represents moderate pain, 7–9 represents severe pain, and 10 represents severe pain. Participants will be allowed to indicate the level of pain by crossing out specific numbers on the scale according to their actual situation. The VAS scale will be administered at week 0, week 4, and month 1.

Traditional Chinese Medicine Syndrome Score Scale (TCMS)

The evaluation of the curative effect of TCMS should refer to the guiding principles of clinical research of new drugs of traditional Chinese medicine and the clinical evidence-based practice guide of traditional Chinese medicine for diabetes. TCMS will be estimated at week 0, week 4, and month 1.

The specific records are as follows:

The VAS score of limb pain was consistent according to the severity.The three main traditional Chinese medicine syndromes of limb numbness, abnormal chill (or fever), and ant feeling were scored as 0, 1, 2, and 3 points, respectively, according to their severity.

Infrared thermography

The test sites will be bilateral plantar, dorsal, palmar, and dorsal hands. The instrument used is the NECR450 infrared thermal imager produced by NECAVIO Company in Japan. Infrared thermography testing will be performed once at week 0 and once at week 4.

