## Discussion

3

As a consequence of the high prevalence of diabetes, DPN is a condition that not only places a load on individuals in terms of their mental burden and financial burden, but it also places weight on society. Most studies focus on acupuncture and electroacupuncture for the treatment of diabetic peripheral neuralgia in both clinical and basic research (16, 30–34), and there is a paucity of research on moxibustion. However, the use of moxibustion in the treatment of diabetic peripheral vascular disease is generally acknowledged in China, and impressive results have been achieved (35). The mechanism of moxibustion in treating DPN may involve the inhibition of NF-kappa B protein and mRNA expression, alongside the induction of Nrf2 protein and mRNA expression in the sciatic nerve, thereby restoring the balance between NF-kappa B and Nrf2 in rats with DPN (36). Moxibustion, although there is a scarcity of clinical studies owing to its operational instability, shows considerable effectiveness in the treatment of diabetic peripheral neuropathy. Therefore, offering a protocol for moxibustion treatment is significant.

Moxibustion, a highly regarded intervention for diabetic complications in China, enjoys popularity, particularly in the fields of rehabilitation and physiotherapy. As of now, the duration of moxibustion for addressing diabetic neuropathic pain remains uncertain and lacks a suitable and standardized protocol. Due to the operation of moxibustion’s lack of standardization, adverse events come and will bring varying degrees of impact on the health of patients such as necrotizing fasciitis (37). The phenomenon described, which pertains to accidents occurring during the moxibustion process, is relatively common. Conditions such as empyrosis, infection, and allergy may arise during surgery due to the prolonged hypoesthesia experienced by diabetic patients, particularly regarding a reduced sense of temperature (38, 39). In this case, it is essential to establish a clinical standard for moxibustion.

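### Safety is checked at each of 8 moxibustion sessions, but the schedule shared by all arms covers only weeks 2 and 4 and leaves month 1 blank

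*Protocol article*

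**What the plan says.** Section 2.10.5 (Safety assessment) has a general rule and one specific to moxibustion. The general rule names no arm: "Detailed records of any adverse events will be maintained, including the adverse event’s onset, symptoms, duration, severity, treatment, and disappearance". The specific rule is: "The safety of moxibustion will be assessed at each treatment session". Incidence is obtained by "recording the number of patients with adverse reactions and dividing it by the total number of patients".

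Section 2.9.2 sets the sessions at "once every three days, twice a week, four consecutive weeks of treatment". The abstract's Methods agree on the number, placing an outcome assessment "after the 8th treatment, and at the one-month follow-up". Section 2.9.1 gives the conventional treatment group oral mecobalamin and epalrestat for 4 weeks and no sessions. Section 2.9.2 gives both moxibustion groups the same two drugs.

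Table 1 (section 2.1) is a single schedule for all arms. Its row "Safety evaluation" is ticked under week 2 and week 4 and is blank under month 1. Total clinical effectiveness, TCSS, VAS and TCMS are all ticked at month 1. Section 2.10.2 confirms this for one of them: "TCSS will be estimated at week 0, week 4, and month 1".

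The Discussion gives the reason for watching harms in this population: "Conditions such as empyrosis, infection, and allergy may arise during surgery due to the prolonged hypoesthesia experienced by diabetic patients".

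**The concern.** Patients who are asked more often report more. All three arms take the same two drugs, so drug reactions and intercurrent complaints can occur in any arm. Eight session checks give the moxibustion arms more occasions for such events to be noticed than the shared schedule gives controls. Part of any difference from control could then reflect how often patients were asked. Patients and treating staff also know the allocation (section 2.8), and the article does not say who makes the session check.

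The second issue is time. A burn complication or an infection can show itself after the last session. Every arm is seen again at month 1, yet no safety evaluation is scheduled for that visit.

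Both are matters of data collection. An event that nobody asked about cannot be recovered at analysis. The abstract's conclusion says the findings could reduce adverse effects, so the harm data are meant to be used.

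**Working it through.** The plan gives no adverse-event rate and no between-arm test of adverse events, so there is no figure of its own to reproduce. The check is a count, a reading of Table 1, and a labelled illustration.

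**Step 1. Count the scheduled safety contacts up to week 4.**
- Moxibustion sessions per arm (section 2.9.2): 2 per week × 4 weeks = 8, which matches the 8 treatments in the abstract.
- Moxibustion sessions in the control arm (section 2.9.1): 0.
- Safety columns ticked for all arms (Table 1): 2, at week 2 and week 4.

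The session rule has no stated counterpart for controls.

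**Step 2. Month 1.** Four outcomes are ticked (total clinical effectiveness, TCSS, VAS, TCMS) and safety is not. The gap is the same in all three arms.

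**Step 3. Which comparisons the asymmetry touches.**
- 15 min versus 30 min: 8 sessions in each arm, so it is unaffected.
- Local events at moxibustion sites: controls cannot have them, so finding them at sessions creates no false excess.
- Non-local events, moxibustion versus control: exposed, because such events can arise in every arm and the scheduled enquiry differs.

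**Step 4. Illustration (all rates assumed).** Let p be the true risk, equal in all arms, and let d be the share of events detected. Observed rate = p × d. False excess = p × (d in moxibustion − d in control). Take d = 0.90 in the moxibustion arms.

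| p | control d = 0.70 | control d = 0.50 | control d = 0.25 |
|---|---|---|---|
| 10% | 9% v 7%: 2 points | 9% v 5%: 4 points | 9% v 2.5%: 6.5 points |
| 20% | 18% v 14%: 4 points | 18% v 10%: 8 points | 18% v 5%: 13 points |
| 30% | 27% v 21%: 6 points | 27% v 15%: 12 points | 27% v 7.5%: 19.5 points |

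For p = 20% in an arm of 30, 4 points is 0.04 × 30 = 1.2 patients and 13 points is 0.13 × 30 = 3.9 patients.

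**Step 5. After the fix.** With the same enquiry in every arm, d is taken as equal and the false excess is p × 0 = 0.

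**The case against.** The strongest case on the other side has five parts.

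- **Recording covers all arms.** The general rule in section 2.10.5 is not limited to moxibustion, and Table 1 applies to everyone. This stands: controls are not left unchecked. But the rule says what is recorded about an event, not when each arm is asked.
- **The ticks may not be a count.** Table 1 also ticks moxibustion treatment only at weeks 2 and 4, although it is given twice weekly. The safety ticks may therefore mark the treatment phase and not two separate contacts. This stands too: it is not established that controls have at most two contacts. What is established is that these two columns are the only scheduled safety evaluation shown for all arms.
- **The session check is a procedural precaution.** The sentence concerns a heat treatment in patients with reduced temperature sense, and no test of adverse events against control is specified. This limits the point to non-local events and to any comparison that is made with control.
- **Known events are followed.** Recording duration and disappearance implies follow-up of events already found. This narrows the month-1 gap to events that are new or first noticed after week 4.
- **A condensed article leaves detail elsewhere.** The case report form or operating procedures may hold more. But the article itself states the session rule and the schedule, so the point rests on what is written.

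A reader might also infer that the incidence formula pools all 90 patients and so dilutes the rate: 6 patients with events would be 6/30 = 20.0% of one arm but 6/90 = 6.7% of the trial. The text does not support this. The primary outcome in section 2.10.1 likewise divides by a total number of cases, and that must be per arm, because section 2.10.4 plans on 60% versus 90% by group. Read the same way, the safety formula is the ordinary incidence proportion.

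**Conclusion.** The point holds in two limited parts.

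1. **Comparability.** A comparison of non-local adverse events between moxibustion and control is open to ascertainment bias, probably against moxibustion. Its size cannot be computed from the document. At a true risk of 20%, the assumed detection rates give 4 to 13 points; over risks of 10% to 30% the range is 2 to 19.5 points. These figures show only what unequal detection could do and rest wholly on the assumed rates.
2. **Completeness.** Harms that arise after week 4 have no scheduled enquiry in any arm, although every arm is seen at month 1. This is not a between-arm bias.

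It would go too far to say that the safety comparison is biased, that controls are never checked, or that the duration comparison suffers from the session asymmetry. The denominator needs clearer wording only.

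**What to change.** - In Table 1, add a safety evaluation at the existing month-1 visit.
- In section 2.10.5, ask the same standard adverse-event question in all three arms at week 2, week 4 and month 1.
- Base any comparison with control on events collected on that common schedule.
- Report the session-level checks separately, as local tolerability of moxibustion, 15 min versus 30 min.
- As a clarification, state that incidence is calculated per arm: patients in that arm with at least one event, divided by patients treated in that arm.

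The cost is one extra question at a visit that already takes place, one tick in Table 1 and a few reworded sentences. The downside is that events found only at session checks are reported outside the comparison with control. If week 2 is not at present a contact for controls, which Table 1 leaves unclear, that enquiry would be an added contact for them.
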